### Study setting and recruitment

We will conduct our research in Beijing, the capital city of China with high population mobility and demographic heterogeneity and high burden of HIV and related STDs among MSM. We will cooperate with a local community-based organization (CBO) named *Man Wellness Center* to recruit participants and provide HIV and other STDs (syphilis, hepatitis B, and hepatitis C) testing services. *Man Wellness Center* is one of the largest and most popular CBO for MSM to give them HIV and STDs prevention and medical services.

Participants will be recruited in two ways: offline and online. The offline recruitment will be implemented in offline venues, such as the clinic sites of the CBO for routine work, and the gay bars, bathrooms, parks for outreach services. The online recruitment will be implemented through online platforms, such as WeChat, QQ, Weibo and Blued. The process of recruitment includes four steps: (1) Determine whether the participant recruited meets the eligibility criteria. (2) Introduce the research and tools for interventions (the app and the WeChat official account) if eligible. (3) Help the participant sign the electronic informed consent through the app and then show him the functions of the app and WeChat official account. The content of the electronic informed consent contains all necessary information as traditional paper version of informed consent, and the signed electronic informed consent will be stored in the database. Participants under the age of 18 are asked to register the app system and sign the consent accompanied by a guardian, and written consent is also obtained from the guardian. (4) Invite the participant to fill in the baseline questionnaire through the app. (5) Provide HIV and other STDs testing services and upload the test results through the backend database. The recruitment will start from the beginning of the research, and we will stop recruitment in the last 6 months of the research. If the participant has HIV and other STDs testing during the follow-up period, he will be invited to finish a follow-up questionnaire.

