The second outcomes of this research include: (1) Positive seroconversion rate (incidence) of syphilis, hepatitis B, and hepatitis C. These indicators are calculated separately as the number of syphilis/hepatitis B/hepatitis C seroconversions divided by the total number of person-years. (2) HIV and related STDs transmission among social networks. Based on the partner notification information, we will construct the transmission networks of HIV and other STDs (syphilis, hepatitis B, and hepatitis C) among participants, and analyze the characteristics of these networks and factors associated with transmission of these diseases. (3) Testing adherence. This indicator is calculated as the proportion of participants whose every adjacent testing interval is no more than 3 months as recommended by China CDC. (4) Additional cost for finding per seroconversion. This indicator is calculated through the total additional cost of the integrated intervention model based on the existing HIV prevention measures provided as before divided by the total number of the HIV and STDs seroconversions. (5) Frequency of utilization for each intervention/service. This indicator is calculated through the total and average frequency of utilization for each intervention/service, such as health education, partner notification, HIV and STDs testing and so on. (6) Satisfaction of the interventions and services, measured through the follow-up questionnaires by the degree of satisfaction for participants of HIV and STDs testing service, health education, partner notification and other app’s functions. (7) Knowledge of HIV and related STDs. This indicator is measured by the baseline and follow-up questionnaires. The score of knowledge questions in the questionnaires will be used to represent participants’ level of knowledge. (8) Health self-responsibility awareness, including attitudes of HIV and STDs testing, safe sexual behaviors and partner notification. The attitudes are collected by questions in the baseline and follow-up questionnaires. (9) Sexual behaviors. They are measured through questionnaires, including questions about the number of different kinds of sexual partners, frequency of anal sex, condom use, and partner notification implementation. (10) Substance use behaviors. This indicator is measured by questionnaires about participants’ usage of methamphetamine, heroin, ecstasy, and some other sex-promoting drugs. (11) Psychological status. Self-rating anxiety scale (SAS) and Self-rating depression scale (SDS) are used to measure participants’ psychological status through questionnaires. (12) Referral rate of HIV and related STDs. This indicator is calculated as the proportion of new HIV and STDs infections who have received treatment. (Additional file 2).

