
### Data management

We developed a data-management platform integrated with the WeChat official account and the app for partner notification. Data are from three sources: (1) HIV and STDs statuses and dates of tests approved and submitted to the management system by the CBO’s staff; (2) baseline and follow-up questionnaires; (3) self-query behaviors (self-query records) and the interactive behaviors (partner notification records) of app users. Participants will be linked through the three date sets by a unique ID, which will be a 16-bit string made up of random letters and numbers transformed from their registered phone number to ensure participants’ privacy.

To protect data security, the data are stored in an encrypted database by a stand-alone server in case of information leakage and illegal use. Hierarchical permissions for CBO’s staff and researchers are set to restrict the viewing and exporting the data. When exporting and analyzing data, all the data will be anonymized. We also set up an independent data management advisory committee to review and evaluate the process of data collection, database management, data analysis, data sharing, and study results.

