### Analysis

Descriptive analysis will be used to summarize the socio-demographic characteristics, HIV and STDs incidences, as well as knowledge, attitudes and related behaviors of total participants and different subgroups. To investigate the effects of the additional partner notification intervention, we will compare the differences of these primary and secondary outcomes in the control period and in the intervention period. As the HIV and STDs infection and most of the secondary outcomes are categorical variables, the generalized linear mixed models (GLMM) will be used for analysis. The model will include intervention status (in intervention period or not) and time as fixed effects and clusters (the districts) and individuals as random effects. The estimated effects of partner notification will be reported as risk ratio (RR) for binary outcomes and mean difference for continuous outcomes. 95% confidential intervals (CI) and *p* values will also be reported. The total and average additional costs of the intervention will be calculated to reflect the cost-effectiveness of the additional interventions, and the differences of these indicators in the control period and intervention period will be compared. Based on the connections recorded in the partner notification records of the database, social network visualization will be conducted to reflect the real connections of the participants. Social network analysis, such as calculation of degree, density, clique, degree centrality, closeness centrality, betweenness centrality, clustering coefficient, and so on, will be used to describe the characteristics of the social networks. Several transmission models of HIV and STDs will be formed to reflect the diseases transmission among MSM.

Sub-analysis will include: comparison of the effects in different age groups, different sex roles (insertive only, receptive only, both), different usage of HIV and STDs testing services (“Mailing rapid test reagent kit” only, the facility-based only, both). A sensitivity analysis will be conducted to evaluate the cluster (the district)-level effect. We will use the outcomes of each district across the follow-ups as the dependent variable, and fit a linear mixed model with the random effect of clusters (the districts).

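### Read plainly, the plan counts enrolment answers from men who join after their district has crossed over as intervention data, which dilutes the effect on the questionnaire-based secondary outcomes

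*Protocol article*

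**What the plan says.** **Source of the outcomes (Outcomes section).** For knowledge (7): "This indicator is measured by the baseline and follow-up questionnaires". For health self-responsibility awareness (8): "The attitudes are collected by questions in the baseline and follow-up questionnaires". For sexual behaviours (9): "They are measured through questionnaires, including questions about the number of different kinds of sexual partners"; substance use (10) and psychological status (11) likewise name questionnaires without a wave. Satisfaction (6), by contrast, is limited to one wave: "Satisfaction of the interventions and services, measured through the follow-up questionnaires by the degree of satisfaction". The Data management section lists the questionnaire data as "2) baseline and follow-up questionnaires".

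**Exposure (Analysis section).** Primary and secondary outcomes are compared between control and intervention periods. For the GLMM: "The model will include intervention status (in intervention period or not) and time as fixed effects". Districts and individuals are random effects. No baseline answer and no indicator of questionnaire wave is listed.

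**Timing (Study setting and recruitment; Study design and timeline).** Step 4 of recruitment is "Invite the participant to fill in the baseline questionnaire through the app". Follow-up questionnaires are offered when a man tests again. The cohort is open, with five 6-month periods and one group of four districts crossing over after each of the first four. On recruitment: "we will stop recruitment in the last 6 months of the research".

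**The concern.** At enrolment a man has been shown the app but has had no real opportunity to use partner notification with a partner. If his district has already crossed over, his baseline answers still fall in an intervention period. Following the stated source and the stated exposure variable therefore puts pre-exposure answers on the intervention side.

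The time effect cannot repair this. It removes what all districts share in a period, whereas the mislabelling sits only in crossed-over districts. It occurs in periods 2-4, the only periods with control and intervention districts side by side.

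At stake are up to five secondary outcomes that serve the protocol's third objective. A real gain in knowledge, awareness or behaviour could be understated or reported as no effect.

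**Working it through.** The plan gives no figure for this quantity. Its 6172 (4320 / 0.70 = 6171.4, rounded up) reproduces and is used below only to turn a share into a count.

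**Inputs from the protocol.** Four groups; crossover at months 6, 12, 18 and 24; end at month 30; recruitment in periods 1-4; ICC 0.01 (set there for HIV incidence, borrowed here).

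**Assumptions, because the protocol does not give them.** Equal group sizes; recruitment pace; form frequency; drop-out pattern; individual correlation 0 or 0.4; baseline forms carry none of the intervention effect; a linear model.

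**Step 1. Entrants whose district has already crossed over.** In periods 1, 2, 3 and 4, the share of groups already crossed over is 0, 1/4, 2/4 and 3/4.
- Even recruitment: (0 + 1 + 2 + 3)/16 = 6/16 = 37.5%, about 2,315 of 6172.
- Weighted 4:2:1:1: (2 × 0.25 + 0.5 + 0.75)/8 = 21.9%.
- Weighted 8:1:1:1: (0.25 + 0.5 + 0.75)/11 = 13.6%.

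**Step 2. Share of baseline forms among intervention forms in period p.** Let r be the recruitment weight of a period, a the mean number of follow-up forms in the entry period, and c the number in each later period. Then

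b_p = r_p / [r_p(1 + a) + c × (sum of r over earlier periods)].

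Forms evenly spaced from an entry date uniform over 6 months give (a, c) = (2.5, 6) monthly, (0.5, 2) 3-monthly and (0, 1) 6-monthly. With even recruitment:

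| Forms | b_2 | b_3 | b_4 |
|---|---|---|---|
| Monthly | 1/9.5 = 11% | 1/15.5 = 6% | 1/21.5 = 5% |
| 3-monthly | 1/3.5 = 29% | 1/5.5 = 18% | 1/7.5 = 13% |
| 6-monthly | 1/2 = 50% | 1/3 = 33% | 1/4 = 25% |

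Over the whole trial, 3-monthly forms give 6/69 = 9% baseline among intervention forms and 10/35 = 29% among control forms.

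**Step 3. Hand approximation of the recovered effect.** Within period p, the contrast between crossed-over and waiting districts recovers 1 − b_p. Weight periods 2, 3 and 4 by the number of pairs of crossed-over and waiting groups (1×3, 2×2, 3×1 = 3, 4, 3):
- Monthly: (3 × 0.895 + 4 × 0.935 + 3 × 0.953)/10 = 0.93.
- 3-monthly: (3 × 0.714 + 4 × 0.818 + 3 × 0.867)/10 = 0.80.
- 6-monthly: (3 × 0.500 + 4 × 0.667 + 3 × 0.750)/10 = 0.64.

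**Step 4. Expectation under the stated model structure.** E(estimate) = (X′V⁻¹X)⁻¹X′V⁻¹μ. X holds period effects and the period-based intervention label. V holds district and individual random effects. μ = 1 for follow-up forms in crossed-over districts and 0 otherwise, so 1.00 means no dilution.

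| Recruitment | Drop-out | Monthly | 3-monthly | 6-monthly |
|---|---|---|---|---|
| Even | none | 0.93 | 0.81 | 0.66-0.67 |
| Even | mean retention 18 months | 0.90 | 0.74 | 0.54-0.57 |
| 8:1:1:1 | none | 0.98 | 0.95 | 0.90-0.91 |

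Weighting of 4:2:1:1 with 3-monthly forms and no drop-out gives 0.90. Weighting of 8:1:1:1 with 6-monthly forms and drop-out gives about 0.85 (individual correlation 0.4). An effect of health education common to both conditions left the ratio unchanged where it was tried.

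The drop-out rows are pessimistic. Exponential retention with mean 18 months loses 1 − exp(−12/18) = 49% by 12 months, whereas the protocol allows 30% loss without stating over what time.

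**The case against.** The best counter-argument is that pooling is inferred. Naming a questionnaire as the instrument does not say that every baseline form is an outcome record labelled by the district's state. The article also speaks of changes in behaviour, which fits a change-from-baseline analysis, and the statistical analysis plan and Additional file 2, neither shown, may settle it. This stands in part: pooling is the plain reading and not an express statement, and for (9)-(11) the use of baseline forms is a further inference. It does not remove the point. The article restricts satisfaction to follow-up forms but not knowledge or attitudes, and its stated model has no baseline term. A more detailed plan written faithfully to this text would inherit the mislabelling.

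A second argument is that the district-level sensitivity analysis is described as using outcomes across the follow-ups. That wording covers only that analysis, so at most it offers a partial check.

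A third is that even recruitment with 6-monthly forms is harsh. Testing prompts are monthly, and adherence is defined by intervals of no more than 3 months. This stands, and it is why the mild scenarios are shown as well.

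A reader might also infer that a raw comparison of control and intervention periods would mislead, since period 1 is rich in baseline forms and period 5 has none. The documents do not specify such a comparison: the description is by total participants and subgroups, and the comparison of periods is tied to a model that includes time.

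**Conclusion.** The concern holds as a flaw in the stated analysis of the questionnaire outcomes: explicit in source for (7)-(8), inferred for (9)-(11). The direction is toward no effect in every scenario examined. The loss runs from about 2% of the true effect (monthly forms, recruitment weighted 8:1:1:1, no drop-out) to about 46% (6-monthly forms, even recruitment, drop-out). No single figure can be claimed, because recruitment pace, form frequency and the timing of drop-out are not in the document.

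A reader might infer that the trial's main result is compromised. The documents do not support that. HIV incidence is seroconversions per person-year and does not use the questionnaires, and the sample size rests on HIV incidence alone. Nor would this dilution create a false claim of benefit.

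**What to change.** State in the Analysis section that outcomes (7)-(11) are analysed on follow-up questionnaires only, with the man's own baseline answer or score for the same item as a covariate. If baseline forms are to stay in the model as repeated measures, code every baseline form as unexposed whatever the state of the district, and add a baseline/follow-up indicator. Under the assumptions above, removing or recoding the mislabelled forms brings the expected ratio back to 1.00.

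The cost is a sentence or two of analysis wording. No new data are needed, and the Trial status section says recruitment had not begun. With the first option, baseline forms no longer count as outcome records, and men with no follow-up form drop out of these analyses. How much precision the baseline covariate would regain was not computed.

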
### Data management

We developed a data-management platform integrated with the WeChat official account and the app for partner notification. Data are from three sources: (1) HIV and STDs statuses and dates of tests approved and submitted to the management system by the CBO’s staff; (2) baseline and follow-up questionnaires; (3) self-query behaviors (self-query records) and the interactive behaviors (partner notification records) of app users. Participants will be linked through the three date sets by a unique ID, which will be a 16-bit string made up of random letters and numbers transformed from their registered phone number to ensure participants’ privacy.

To protect data security, the data are stored in an encrypted database by a stand-alone server in case of information leakage and illegal use. Hierarchical permissions for CBO’s staff and researchers are set to restrict the viewing and exporting the data. When exporting and analyzing data, all the data will be anonymized. We also set up an independent data management advisory committee to review and evaluate the process of data collection, database management, data analysis, data sharing, and study results.

### Analysis

Descriptive analysis will be used to summarize the socio-demographic characteristics, HIV and STDs incidences, as well as knowledge, attitudes and related behaviors of total participants and different subgroups. To investigate the effects of the additional partner notification intervention, we will compare the differences of these primary and secondary outcomes in the control period and in the intervention period. As the HIV and STDs infection and most of the secondary outcomes are categorical variables, the generalized linear mixed models (GLMM) will be used for analysis. The model will include intervention status (in intervention period or not) and time as fixed effects and clusters (the districts) and individuals as random effects. The estimated effects of partner notification will be reported as risk ratio (RR) for binary outcomes and mean difference for continuous outcomes. 95% confidential intervals (CI) and *p* values will also be reported. The total and average additional costs of the intervention will be calculated to reflect the cost-effectiveness of the additional interventions, and the differences of these indicators in the control period and intervention period will be compared. Based on the connections recorded in the partner notification records of the database, social network visualization will be conducted to reflect the real connections of the participants. Social network analysis, such as calculation of degree, density, clique, degree centrality, closeness centrality, betweenness centrality, clustering coefficient, and so on, will be used to describe the characteristics of the social networks. Several transmission models of HIV and STDs will be formed to reflect the diseases transmission among MSM.

Sub-analysis will include: comparison of the effects in different age groups, different sex roles (insertive only, receptive only, both), different usage of HIV and STDs testing services (“Mailing rapid test reagent kit” only, the facility-based only, both). A sensitivity analysis will be conducted to evaluate the cluster (the district)-level effect. We will use the outcomes of each district across the follow-ups as the dependent variable, and fit a linear mixed model with the random effect of clusters (the districts).

If one variable is missing for < 10% of participants, we will use a complete-case approach. If one variable is missing for 10 ~ 20% of participants, multiple imputation will be used if suitable; if one variable is missing for > 20% of participants, we will investigate the mechanism of missing data, and consider to set the missing data as a category.

A two-sided *p* value of 0.05 or less was regarded as significant. Statistical analyses will be done with SPSS version 21.0, Stata version 24.0, R version 3.5.1. Social network visualization will be done with Cytoscape version 3.5.1.

The results of this research will be reported to local and national stakeholders in the form of oral presentation on professional conferences and publications on journals. We will not use professional writers in writing related articles and reports. The decisions of authorship will follow conventions of the International Committee of Medical Journal Editors. We will share our study protocol, statistical analysis plan, informed consent form, study report and analytic code after completing the analysis of the whole study. If other researchers want to apply for the above information and data of this research, they should contact principal investigator. Personal information (name, unit, title, etc.), detailed description of required data (required variables, etc.), and research proposal are needed for further discussion and decision.

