## Methods/design

### Study design and timeline

This research will use a stepped wedge cluster randomized controlled trial (SW-CRCT) design. It is commonly used to evaluate service delivery or policy interventions of clusters [26]. This research will be implemented in Beijing, whose sixteen districts are defined as the clusters. We assign the sixteen districts into four research groups using stratified randomization, with four districts in one group. The open cohort SW-CRCT will last 2.5 years, which is anticipated to be conducted from July, 2020 to December, 2022. Five continuous observational periods at a 6-month interval are divided. According to the standard design of SW-CRCT, in the first 6-month “the initial period”, no group is exposed to the additional partner notification intervention. After that, the four groups begin to cross from the control condition to receive the partner notification intervention sequentially at 6-month intervals. Once one group receives the partner notification intervention, the intervention will continue until the end of the research. And at the last 6-month period, all of the four groups will receive the additional partner notification intervention. (Fig. 1).

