## Discussion

One important reason that HIV keeps increasing among MSM in China is that most MSM seeking causal sexual partners through online dating platforms (such as Blued and Zank), as it results in much more risk sexual behaviors for HIV and other STDs transmission [30, 31]. Partner notification of HIV and STDs infection statuses before they decide to meet and have sex can be an important and feasible method to reduce the HIV and STDs transmission among sexually active MSM. China’s Internet penetration rate has reached 61.2% by June 2019, and 99.1% of Internet users use mobile phones to surf the Internet [32]. The intervention tools based on the WeChat-the most popular mobile phone social software [33], and a website-based app enable the method more acceptable, convenient and intimate for MSM. It may lead to better effects compared with the existing partner notification methods provided by health workers individually or through email cards. An observational study using the previous version of this app has shown a potential positive effect of the app-based partner notification intervention in reducing HIV infection among MSM [29]. An encouraging finding was that the longer the app was used, the lower the HIV incidence (> 5 months vs ≤ 5 months: 2.22 per 100 person-years vs 6.99 per 100 person-years; risk ratio 0.32, 95% CI 0.12–0.87), and the app has also been proved to be user-friendly and could be accepted and widely used by MSM [29]. However, the blank control without receiving the partner notification intervention was lacking in the observational study. Meanwhile, the observation period was only 1 year and the sample size was small, so the effectiveness of the intervention needs to be further evaluated by this trial.

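### The stated model for this open cohort has one undefined time term and none for time since enrolment, so the HIV risk ratio is biased if incidence depends on time since enrolment and recruitment pace shifts in opened relative to closed districts

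*Protocol article*

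**What the plan says.** The Analysis section describes the GLMM for HIV and STD infection and most secondary outcomes: "The model will include intervention status (in intervention period or not) and time as fixed effects", and "clusters (the districts) and individuals as random effects". It does not say whether time is calendar period or time since joining, and it names only one time term.

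Under Study design and timeline, "The open cohort SW-CRCT will last 2.5 years", in five 6-month periods with the four groups crossing in turn. Under Study setting and recruitment, "The recruitment will start from the beginning of the research, and we will stop recruitment in the last 6 months of the research". Enrolment therefore runs over months 0 to 24, spans the first three crossovers and ends at the fourth.

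Under Intervention implementation, men in control time also use the app from enrolment (education, testing prompts, self-query); only partner notification is closed.

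The Discussion reports from an observational study of an earlier app version that "the longer the app was used, the lower the HIV incidence": for more than 5 months against 5 months or less, "2.22 per 100 person-years vs 6.99 per 100 person-years; risk ratio 0.32, 95% CI 0.12–0.87". It also concedes that "the blank control without receiving the partner notification intervention was lacking in the observational study".

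**The concern.** Two clocks may drive HIV incidence here. One is calendar period, which the roll-out follows by design. The other is time since a man joined. If rates are high in the first months after joining and lower later, a district's rate in any period depends partly on its mix of recent and long-standing participants.

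Categorical period effects remove this only when open and closed districts have the same mix within each period. If opening partner notification brings in more new men, open districts carry more early, high-rate person-time and the intervention looks weaker than it is. If recruitment slows after opening, a spurious benefit appears.

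A random intercept per man does not solve this, because it is constant over time and seroconversion happens once. Baseline covariates do not solve it either, because men who are identical at baseline can differ in how long they have been in the cohort. If the one time term meant follow-up time instead, calendar trend would be left unadjusted.

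**Working it through.** **The pilot figure.** 2.22/6.99 = 0.318, which agrees with the stated 0.32. The geometric midpoint of the interval is √(0.12 × 0.87) = 0.323. The gradient is 6.99/2.22 = 3.15-fold, and the interval allows 1/0.87 = 1.15-fold to 1/0.12 = 8.3-fold.

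**Inputs from the protocol.** Four groups crossing at months 6, 12, 18 and 24; enrolment in months 0 to 24; follow-up to month 30; planned effect 5/7 = 0.714; power 0.90; two-sided 0.05.

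**Assumptions not in the protocol.** Even recruitment before opening, 2% loss per month, a pace multiplier r in a group once it opens, and the pilot gradient applying by time since enrolment under both conditions.

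**Method.** For each group and period, expected events = person-years within 5 months of enrolment × 0.0699 + later person-years × 0.0222, multiplied by the true risk ratio after opening. A Poisson model with intervention, period and group terms and a person-year offset is fitted to these expected counts. Group fixed effects stand in for the random effects.

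**Equal pace.** Without loss, the share of person-time within 5 months of enrolment is 0.95, 0.53, 0.32, 0.23 and 0.07 over the five periods. It is the same in every group, so the period terms absorb it: the model returns 1.000 and 0.714. A doubling in all districts at once at month 12 also gives 1.000.

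**Pace shifting at opening.** At r = 2 without loss, the early share in period 2 is 0.64 in the opened group and 0.53 in the closed ones. That difference produces the bias.

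| r | Estimate, true 1.00 | Estimate, true 0.714 | True 1.00, half the log gradient |
|---|---|---|---|
| 0.67 | 0.938 | 0.670 | 0.969 |
| 1 | 1.000 | 0.714 | 1.000 |
| 1.25 | 1.040 | 0.743 | 1.020 |
| 1.5 | 1.076 | 0.768 | 1.037 |
| 2 | 1.137 | 0.811 | 1.067 |

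Without loss, the null values at r = 1.25, 1.5 and 2 are 1.039, 1.074 and 1.135, so the loss assumption hardly matters. With the gradient at its interval limits and no loss, doubling gives 1.015 (gradient 0.87) to 1.240 (gradient 0.12).

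**Power.** Power = Φ(3.24 × ln(estimate)/ln(0.714) − 1.96), with the standard error held at its planned value. For r = 1.25, 1.5 and 2 the nominal 90% becomes about 82%, 72% and 52%. If the extra men add to the total sample, it is about 84%, 76% and 60%.

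**With the added term.** Including 5 months or less vs more than 5 months since enrolment returns 1.000 and 0.714 at every r. The standard error of the intervention term rises by at most 0.2%, and not at all at equal pace.

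**The case against.** The strongest objection is that the protocol establishes neither condition.

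A reader might infer from the Discussion that incidence falls three-fold with time on the app whatever the condition. The text does not support that. It introduces the figures thus: "An observational study using the previous version of this app has shown a potential positive effect of the app-based partner notification intervention". Those men had partner notification, the study was small, and it had no group without the function. The sample size section also plans 7% in control status, whereas the full gradient under the assumptions above implies a mean control rate of about 4.6 per 100 person-years. This stands: the gradient under control is an assumption. But an uncontrolled comparison cannot credit the whole fall to partner notification either.

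A reader might also infer that any change in recruitment pace biases the result, or that a change is expected. Neither follows. Shared changes are absorbed by categorical periods, and no section says pace will differ between open and closed districts. Opening is automatic and staff are not told of it; one organisation recruits across the city; status requests are not described as confined to one district. Against that, participants will see the new function, it is useful only if partners are in the system, and recruits are shown the app's functions. A shift is possible, more plausibly upward (towards the null) than downward.

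It can also be said that coding of time belongs in the analysis plan, which is not shown and may define it. That is fair for the coding. The article does, however, list the fixed effects, and one time term cannot cover both clocks.

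Finally, if the gradient follows months of partner notification exposure, the added term does not cure the resulting distortion. With control flat at 6.99, the estimate at equal pace is 1.09 with or without it; at double pace it moves from 1.14 to 1.08, and at half pace from 1.06 to 1.085. That delayed-effect question is separate.

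**Conclusion.** The point holds as a conditional one. The stated model omits time since enrolment in a cohort that enrols across the roll-out. The primary risk ratio is biased only if incidence depends on time since enrolment under both conditions and recruitment shifts in opened relative to closed districts within the same period. For a pace change between 0.67 and 2, the shift under the null runs from 6% downward to 14% upward with the full pilot gradient, and from 3% downward to 7% upward with half of it on the log scale. At the weak limit of the pilot interval, even doubling moves it by only 1.5%. The protocol does not show that the bias will occur. The change is worth making because it removes the risk at almost no cost.

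**What to change.** In the models for HIV, syphilis, hepatitis B and hepatitis C incidence:

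- Define time as calendar period and enter it as a categorical fixed effect.
- Add time since enrolment as a second, time-varying fixed effect (for example 5 months or less vs more than 5, or 6-month bands).
- Split each man's person-time at his district's crossover date and at the band limits.
- Report new enrolments by district and period beside the primary result, so that readers can see whether pace shifted.

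The cost is one to four degrees of freedom and a negligible loss of precision, using enrolment and test dates that the trial already holds. The term does not address a delayed effect of partner notification, which needs its own treatment.
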